**Fig. 2 Fig2:**
[figure not shown]
Virtual Reality scenarios of the CRAVE VR paradigm. **A**: VR acclimation room before starting the exposure session. **B**: Bar 1, a corner pub. **C**: Living room; patients choose one of the drinks depicted here before starting the VR exposure. **D**: Neutral VR scenario (baseline). **E**: Barkeeper in Bar 1, bringing a beer. **F**: Bar 2, an elegant wine bar

#### Outcomes

Primary outcomes of the study are changes in craving levels measured by psychophysiological parameters (HR, HRV with special focus on HF-HRV, EDA, pupillometry) and subjective parameters (VAS) before, during and after VR-exposure to alcohol-associated cues compared to neutral cues.

Secondary outcomes are a) changes in subjective and objective craving levels compared between the two VR-scenarios bar vs. living room, b) the changes of subjective craving over the following 3 h after VR-exposure, c) measures of the sense of presence (scores of IPQ), d) measures of motion sickness assessed with the Fast Motion Sickness Scale.

#### Data management and monitoring

Clinical data and questionnaires will be collected using REDCap electronic data capture tools hosted at Charité—Universitätsmedizin Berlin [41, 42]. Data will be pseudonymized by unique identification codes for every patient entering the study. The reidentification list will be kept in a secure environment and only study responsible staff will have access. According to good scientific practice, the primary data are kept for ten years after publication. Data will be made available via the open science framework in a de-identified format and in the appendix of the final publication.

The highest possible data protection standards and secure data transmission protocols will be established following the EU General Data Protection Regulation and the Berlin Data Protection Act. The data will be stored on a designated server. All participants are entitled to inspect the data collected and/or to request the blocking or deletion of their data until deletion of the reidentification list.

#### Sample size

In previous studies on related topics, alcohol-associated cues compared to neutral cues show small to moderate effects on different psychophysiological parameters (0.2 < Cohen’s d < 0.39) and on subjective craving (Cohen’s d ~ 0.45) [6]. These previous studies used isolated “in vivo” stimuli. Due to a higher ecological validity of VR scenarios, we expect larger effects regarding the psychophysiological parameters (Cohen’s d = > 0.4). The sample size calculated in G-Power for computing ANOVA assuming an alpha error of 0.05 and a test power of α = 0.8 is *n* = 52. Assuming a drop-out rate of approximately 15%, 60 patients should be recruited to ensure sufficient statistical power.

#### Statistical methods

Statistical analyses are planned to be conducted using the software SPSS (SPSS Inc., Chicago, IL, United States). Growth-curve mixed models will be used to examine the effect of the three scenarios as within subject-condition (neutral, living room, bar) on physiological and subjective craving parameters. To address the change of subjective craving following the exposure, growth-curve mixed models will be used to examine the effect time (follow-up immediately, after 1, 2 and 3 h after VR exposure as within subject-factor with 4 levels) on craving levels as assessed by VAS.

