### Primary hypothesis

We hypothesize that exposure to alcohol-related scenarios in VR will elicit a transient increase in craving in patients with AUD, measurable with subjective and physiological parameters compared to exposure in a neutral VR environment.

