### Data collection

#### Clinical data and questionnaires

General baseline data are collected in interviews before the VR exposure. These potentially confounding variables include demographic data (socioeconomic status), age, gender, medical history and comorbidities. Screening interviews include the Alcohol Urge Questionnaire (AUQ, [27]), Obsessive Compulsive Drinking Scale (OCDS, [28]) and Craving Automated Scale for Alcohol (CAS-A, [29]) to ensure the capability of perceiving and indicating subjective craving in patients. Severity of alcohol dependence will be measured with the Alcohol Use Disorder Identification Test (AUDIT, [30]), the Alcohol Dependence Scale (ADS, [31, 32]) and the Lifetime Drinking History (LDH, [33]). VAS scores (scores from 0–100)—the international standard measurement of subjective craving [34]—will be assessed before, during (3 times during each VR environment, minutes 00:30, 02:30, 04:30, 05:30, 07:30, 09:30, 10:30, 12:30, 14:30, 15:30, 17:30, 19:30) and directly after the VR exposure (min. 20:30). Furthermore, we will assess VR-specific side effects (kinetosis) using the Fast Motion Sickness Scale [35] during VR exposure. To study the short-term effects of VR exposure on craving, participants will indicate their craving level every hour for 3 h after exposure on a VAS and via the AUQ. To evaluate the feeling of “presence” during VR exposure, participants will be asked to complete the Igroup Presence Questionnaire (IPQ, [36, 37]) after completing VR exposure. The assessment of clinical data and questionnaires is estimated to take approximately 90 min. (Fig. 1; Workflow).

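### No stated analysis compares the 0 to 3 h follow-up VAS readings with the pre-exposure VAS, so craving duration and return to the starting level go untested

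*Protocol article*

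**What the plan says.** All references are to the protocol article.

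- **Primary hypothesis:** alcohol-related VR scenes "will elicit a transient increase in craving in patients with AUD", with a neutral VR environment as comparator.
- **Exploratory objectives:** one of them is to assess how long craving lasts over the first 3 h after exposure.
- **Outcomes:** the primary outcome covers craving "before, during and after VR-exposure to alcohol-associated cues compared to neutral cues". Secondary outcome b is "the changes of subjective craving over the following 3 h after VR-exposure".
- **Clinical data and questionnaires:** VAS scores "will be assessed before, during (3 times during each VR environment", at 12 listed times), and again directly after exposure at min 20:30. After that, "participants will indicate their craving level every hour for 3 h after exposure on a VAS and via the AUQ".
- **Statistical methods, first model:** growth-curve mixed models will "examine the effect of the three scenarios as within subject-condition (neutral, living room, bar) on physiological and subjective craving parameters".
- **Statistical methods, second model:** "To address the change of subjective craving following the exposure, growth-curve mixed models will be used to examine the effect time" on VAS craving. Its time factor is specified as "follow-up immediately, after 1, 2 and 3 h after VR exposure as within subject-factor with 4 levels".

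**The concern.** To say how long craving lasts, one needs a level at which it counts as over. The natural reference is the patient's own VAS before exposure, which is collected. The second model contains only readings taken after exposure, so it can compare them with one another but not with the starting point. The first model names three scenes and no follow-up reading. The pre-exposure VAS, although part of the primary outcome's time frame, has no place in either stated analysis.

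What is at stake is the interpretation of the follow-up curve. A significant fall over 3 h could end above, at or below the level at which patients arrived, and these are different statements about duration. If the reference is chosen after the curve has been seen, the answer is post hoc.

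**Working it through.** **1. Readings collected against readings modelled**

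| VAS reading | Collected | Scenario model | Follow-up model |
|---|---|---|---|
| Before exposure | yes | not named | not a level |
| During the scenes (12 readings) | yes | yes | no |
| Directly after (min 20:30) | yes | not named | level 1 |
| 1, 2 and 3 h | yes | not named | levels 2 to 4 |

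No row before exposure is joined to a row after exposure in the same model.

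**2. What the four-level time effect can see**

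Let m0, m1, m2, m3 be the mean VAS at 0, 1, 2 and 3 h, and b the pre-exposure mean. The time effect tests m0 = m1 = m2 = m3. It depends only on differences such as m3 - m0. Adding a constant c to all four means leaves (m3 + c) - (m0 + c) = m3 - m0, so only the intercept moves. The quantity needed for return is m3 - b (and likewise m1 - b and m2 - b). Since b is not in the model, the test cannot depend on it.

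**3. Illustration (assumed values, not document figures)**

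n = 52, VAS SD 20, correlation 0.5 between any two readings, true post-exposure means 40/32/28/25, one simulated data set. Only the true pre-exposure mean is varied.

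| True pre mean | Four-level time test | Immediate minus pre | 3 h minus pre |
|---|---|---|---|
| 10 | F = 8.56, p = 0.00003 | t = 13.3 | t = 7.5 (still raised) |
| 25 | F = 8.56, p = 0.00003 | t = 6.9 | t = 1.6, p = 0.12 (no clear difference) |
| 40 | F = 8.56, p = 0.00003 | t = 0.5 | t = -4.4 (below the start) |

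One planned result is thus compatible with three different answers about duration.

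**4. Why a non-significant contrast is not enough**

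In the middle row the simulated 3 h mean is 31.3 and the pre mean 27.4, a difference of 3.9. With t = 1.56, the standard error is about 3.94/1.565 = 2.52. The 95% CI is 3.94 ± 2.008 × 2.515, or -1.1 to 9.0 VAS points. The p-value of 0.12 does not by itself establish return; whether 9 points above the start is excluded or tolerable depends on a margin.

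**5. Precision available without new data**

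Half-width of the 95% CI for a post-minus-pre difference = 2.008 × SD × √(2(1 - ρ))/√n. With SD 20 and n = 52:

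- ρ = 0.3: 2.008 × 23.66/7.21 = 6.6 points
- ρ = 0.5: 2.008 × 20.00/7.21 = 5.6 points
- ρ = 0.7: 2.008 × 15.49/7.21 = 4.3 points

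**6. Sample size**

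The stated n = 52 is reproduced by a paired two-condition contrast at d = 0.4, two-sided alpha 0.05 (sidedness is not stated), with power 0.808. It does not rest on the follow-up model, so the change proposed here does not alter it.

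**The case against.** The strongest reply is that each model does its own job. The hypothesis and the primary outcome set neutral VR as the comparator for the rise, and the scenario model tests exactly that. The follow-up model matches secondary outcome b as worded, and a fall from the immediate reading is itself part of being transient. All of this stands, and it rules out three stronger readings:

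- **That the plan cannot show that craving rose.** A reader looking only at the four-level factor might infer this. It is true of that model alone; the scenario model tests the rise against the stated comparator.
- **That craving never raised and craving raised throughout would be indistinguishable.** Both would give a flat follow-up curve, but the scenario model would differ between them. Read together, the two models partly separate these cases.
- **That leaving out scenario order is an error.** The min 20:30 reading follows whichever risk scene came second, but the order is randomised, so the average curve remains interpretable. An order term is a detail commonly left to a fuller plan.

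It can also be said that the second neutral-room period, after a break of up to 45 min, offers another reference. No stated model links it to the 1 to 3 h readings either, and it comes after the first risk scene, so it is not a clean starting level.

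Finally, an article condenses a longer plan. That would explain silence about the time factor. Here the levels are listed and counted, and a plan with the pre-exposure reading as a further level would contradict the sentence. A pre-exposure covariate would not contradict it, but none is mentioned.

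**Conclusion.** The concern holds in a limited form. As stated, no analysis relates the 0, 1, 2 and 3 h VAS readings to the pre-exposure VAS, so the plan does not show whether or when craving returns to its starting level. The craving-duration objective and the return part of a transient increase are not answered. The test of the rise against neutral VR, secondary outcome b and the sample size are not affected.

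The argument in step 2 needs no assumed figures. The sizes in steps 3 to 5 rest on an assumed SD, correlations and means, and serve only to show scale. Because the objective is exploratory, this should be fixed but does not threaten the main comparison.

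**What to change.** Define the follow-up time factor with five levels (pre-exposure, immediately after, 1, 2 and 3 h), with the pre-exposure VAS as reference. Report each of the four post-minus-pre differences with its 95% CI. State in advance that return is judged from the estimate and its CI, ideally against a VAS margin set by the investigators before the data are seen, and not from a non-significant difference. A change score from the pre-exposure VAS would be an acceptable alternative way of making the link. A term for scenario order may be added but is optional.

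The cost is one or two sentences in the analysis plan, written before analysis starts. The reading is already scheduled, the time effect uses 4 degrees of freedom instead of 3, and no extra patients are needed.

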#### Patient and public involvement

Patients were involved in study planning by stating appropriate stimuli in five anonymous clinical interviews on the ward for Treatment of Addiction Disorders in the Psychiatric University Hospital Charité at St. Hedwig-Hospital.

## Discussion

This is the first study examining change in several psychophysiological craving parameters in patients with AUD using VR exposure.

Results shall lead to a better understanding of the induction of craving in VR cue exposure as well as the link between subjective and physiological parameters. This could offer new diagnostic and therapeutic perspectives, e.g., providing a basis for future biofeedback training in VR exposure therapy. Since evidence on the effectiveness of CET in AUD is still limited [9, 10] and the role of habit learning in addictive disorders has been discussed (e.g. Hogarth et al. [43]), it would be valuable to discriminate subgroups with pronounced cue-reactivity who could potentially profit even more from this treatment. On an exploratory basis, the comparison between craving levels in the bar versus home situation will help to define contexts with pronounced craving, helping to better understand the role of social cues in inducing craving. As regards the direct benefit for patients, the VR experience in this study and future VR application can be an individually tailored tool to identify high-risk situations and practice coping skills.

This study is limited by a single-arm design: The study design does not allow a comparison of the elicited craving between patients and healthy controls. This would have changed the focus and research question of the study but would certainly be of interest for further studies in this field.

## Data Availability

The datasets used and/or analysed during the current study are available from the corresponding author on reasonable request.

## Abbreviations

AUD: Alcohol use disorder
VR: Virtual reality
GDP: Gross domestic product
CET: Cue-exposure therapy
CBT: Cognitive behavioral therapy
HMD: Head-mounted display
SUD: Substance use disorder
AUQ: Alcohol Urge Questionnaire
VAS: Visual analogue scale
AUDIT: Alcohol Use Disorders Identification Test
OCDS: Obsessive Compulsive Drinking Scale
CAS-A: Craving Automated Scale for Alcohol
LDH: Lifetime Drinking History
IPQ: Igroup Presence Questionnaire
HR: Heart rate
HRV: Heart rate variability
EDA: Electrodermal activity
